### Quantitative analysis

Descriptive statistics will summarize baseline characteristics overall and by study arm (i.e., usual family support services vs. MB-VG). As appropriate, mean ± standard deviation (or median [inner quartile range]) will be used in cases of skewed or non-normal empirical distributions and frequency (proportions) will summarize continuous and categorical data, respectively. Analyses will employ normal theory methodology as appropriate, and in cases of violations of assumptions, transformations, and/or nonparametric analyses may be utilized. Analyses will proceed at the participant level, and all hypothesis tests will assume a two-sided 5% level of significance. We will apply the Benjamini–Hochberg correction to control family-wise type I error rate to 5%. We plan to perform all analyses using both the intent-to-treat (ITT) approach and a dose–response approach, adjusted for propensity scores. Multilevel analysis, i.e., generalized mixed effects models, will estimate baseline and multivariate adjusted between-group differences, adjusted odds ratios (AORs), and 95% confidence intervals (CIs) using individual-level data but considering the hierarchical and clustered structure of data, with participants clustered by group (i.e., Judy Center). We believe clustering by group will be very small and thus do not take it into account in the power analysis. Doing so would lead to a small increase in the minimal detectable effect sizes (e.g., increasing from 0.241 to 0.284). Continuous outcomes will use a model that assumes normally distributed outcomes, and appropriate transformations of the data will be made to improve normality. Binary outcomes will be assessed using a logistic regression-based multilevel model.

*Effectiveness outcomes*: Aim 1 will be tested by examining the coefficient of the treatment vs. control indicator in the random effects model. We will include random intercepts for group and instructors and will also investigate whether a random slope for group is appropriate for the intervention effect. Intervention group, covariates measured at pretest (especially the pretest measures of the outcome, as available), the Judy Center the participant was recruited from, and instructor characteristics will be included as fixed effects. Likelihood ratio tests (significance criterion, *p* < 0.05) will be used to simplify the models following a backward selection strategy. Although the primary analyses will consider each set of follow-up outcomes separately, controlling for pre-test measures in each analysis, we will also consider the use of longitudinal growth models to model the growth in knowledge over the three time points. Primary endpoint #1 is depressive symptoms, as measured by the Center for Epidemiologic Studies-Depression scale (CES-D). A total continuous score (0–60) is calculated for the CES-D. Primary endpoint #2 is depressive episodes as measured by the SCID. The SCID is used to assess the presence/absence of major depression, making it a binary outcome (yes/no). Primary endpoints #3 and #4 are parenting self-efficacy measured via the PACOTIS and parenting responsiveness measured via the MIRI and PCOS (used as a separate coding system when coding the DB-DOS observation assessment). A mean score is calculated for each of the PACOTIS and MIRI subscales. Secondary endpoint #1 is anxiety symptoms, measured via the GAD-7. A total continuous score is calculated for the GAD-7. Secondary endpoint #2 is perceived stress, measured via the PSS-10. A total continuous score is calculated for the PSS-10.

Covariates will be finalized in a Statistical Analysis Plan but based on our prior studies [80, 87] will include (1) whether participant is a first-time mother (e.g., current number of children = 0 at baseline; (2) education (at least some high school vs less than high school); (3) mental health service utilization (we will control for enrollment with a therapist for counseling at baseline and medication for depression at baseline).

Outliers will be assessed to determine whether it is a data entry error or some other protocol error. If not, sensitivity analyses will be conducted to assess the impact of the outliers. Because this is an intent-to-treat analysis, non-adherence will not be formally dealt with. Reasons for loss to follow-up will be explored and we will determine if any key factors contributed to dropout or attrition. Results of initial analyses will determine the best method to handle missing data in the main study analyses.

Analysis of the secondary endpoints will be examined in a manner like those described above related to analysis of our primary endpoints. Primary and secondary outcomes will be assessed utilizing mixed effects logistic regression (when outcomes are binary) and mixed effects linear regression (when outcomes are continuous). Subgroup analysis will follow the same analytic protocol, beginning with the addition of an interaction term between intervention status and the subgroup variable. This will be followed by multiple group analysis.

For *Implementation Outcomes*, mean scores of Acceptability of Intervention Measure, Implementation Appropriateness Measure, and Feasibility of Intervention Measure will be calculated for each perinatal participant and facilitator participant to assess MB-VG *acceptability, appropriateness*, and* feasibility*, respectively. We will use descriptive statistics to examine variability in implementation outcomes by respondent type and participant characteristics. We will examine variability in session attendance and utilization of Resource Advocate by participant characteristics. *Fidelity* will be calculated via a mean adherence and competency rating for each rated session with linear mixed models used to evaluate site, participant, and facilitator characteristics’ influence on these outcomes. *Adaptation* will be calculated using descriptive statistics to assess frequency of adaptations with latent class analysis examining whether adaptations group together in underlying patterns across facilitators or Judy Centers. *Cost* implementing MB-VG will be generated by deriving a per-hour salary estimate for each facilitator, Resource Advocate, and pediatrician. When possible, we will obtain actual salaries (see baseline survey for facilitator participants and for director participants); if these salaries are unavailable, we will use state-specific salary estimates based on position title and degree from the Bureau of Labor Statistics for the relevant year. We then will multiply wage rates plus fringe benefits by the time spent engaged in MB training and delivery. Once total costs are calculated, we will calculate a per-organization and per-participant cost of MB-VG. We will aggregate labor and non-labor cost data to measure the cost of implementation from a societal perspective inclusive of organization and participants, as well as reported separately by group. *Maintenance* will be calculated by generating mean scores for the overall SMSS and each of its domains.

*Exploratory outcomes*: We will conduct analyses related to our exploratory objective assessing child dysregulation and school readiness among children aged 2.5–4.5 years. For the Disruptive Behavior Diagnostic Observation Scale (DB-DOS), we will conduct a series of ANOVAs examining differences between intervention and control children on each DB-DOS subscale: anger modulation, behavioral regulation, and competence. For the Bracken School Readiness Composite, we will conduct an ANOVA comparing intervention and control children on their overall school readiness composite score.

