### Missing data

Sample size and power calculations were completed under the assumption of 20% attrition for primary outcome analyses. Thus, while we anticipate missing data, we still expect adequate power to detect differences between study arms. We will examine rates of missing data for all variables and determine whether rates vary by participant characteristics, Judy Center program, or study arm. These analyses will indicate the extent to which missing data could bias results. We will attempt to collect data at each time point regardless of participants’ engagement in earlier data collection efforts. To minimize missing data due to loss to follow-up, we will devote considerable attention to promoting study retention. The planned mixed effects models are generally robust for unbalanced data across study time points. However, we plan to apply multiple imputation to test for bias introduced by missing data in sensitivity analyses; we will impute at least five datasets to generate an estimated average intervention effect.

We plan to perform all analyses using both the intent-to-treat (ITT) approach and a dose–response approach (treating dosage as a continuous variable of 0–10 sessions attended), adjusted for propensity scores. The dose–response approach will examine the relationship between number of MB-VG sessions attended (dosage) and outcomes, using propensity scores to match intervention participants to control-group participants with a similar propensity to take up a given level of intervention. This will reduce the influence of self-selection bias in intervention take up on the estimates of dosage effects. We plan to stratify analyses by whether participants are prenatal vs postpartum and whether participants are primiparous or multiparous.

Interim analysis will be performed to ensure safety. This analysis will focus on whether participating in the intervention has any significant iatrogenic effects. Individuals who score > 40 on the CES-D at any assessment timepoint will be flagged, since this level of symptomatology can be considered “very severe”; these participants will be contacted by the research team per procedures described below in the " Safety considerations and procedures" section. The safety analysis dataset will include those participants who had at least one session of the study intervention. No other formal planned interim analyses are planned.

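### Benjamini–Hochberg is said to control the family-wise type I error at 5%, but it controls the false discovery rate, so the stated family-wise guarantee does not hold in general

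*Protocol article*

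**What the plan says.** In the protocol article, under Quantitative analysis, the multiplicity statement reads "We will apply the Benjamini–Hochberg correction to control family-wise type I error rate to 5" per cent. The sentence before it says that "all hypothesis tests will assume a two-sided 5% level of significance". The article does not mention the false discovery rate, names no other multiplicity procedure and does not say which tests form the family.

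The effectiveness paragraph of the same section names four primary endpoints. The first is the CES-D score. For the others: "Primary endpoint #2 is depressive episodes as measured by the SCID", and "Primary endpoints #3 and #4 are parenting self-efficacy measured via the PACOTIS and parenting responsiveness measured via the MIRI and PCOS". On visits it says that "the primary analyses will consider each set of follow-up outcomes separately".

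Table 2 schedules the CES-D at three follow-ups, the SCID, PACOTIS and MIRI at 3 and 6 months, and the PCOS at 6 months only. The abstract places the CES-D, PACOTIS and MIRI at all three follow-ups and the SCID at two.

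The Statistical analysis section gives detectable effects of 0.241 with 300 women and 0.269 after about 20% attrition. Both are at two-sided alpha 0.05, and no multiplicity adjustment is mentioned.

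**The concern.** Family-wise control at 5% means that the chance of any false positive in the family is at most 5%, whichever nulls are true. Benjamini–Hochberg bounds something else: the expected share of false positives among the rejections. The two coincide when every null is true, because any rejection is then false. Once real effects are rejected, the procedure loosens the threshold for the remaining tests. That is acceptable for the false discovery rate but not for the family-wise error.

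A mixture of real and null effects is the plausible case here. The hypotheses under Study aims predict effects on symptoms, cases of postpartum depression and parenting, and the power section expects small to moderate effects. If the intervention lowers CES-D scores but does not change parenting, a chance parenting result would be judged against a loosened threshold. It would still be reported as protected at 5% family-wise. This is the only multiplicity control stated for the primary claims.

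**Working it through.** **1. Possible families.** The document defines none, so I counted the candidates.
- All endpoint-by-visit tests by Table 2: CES-D 3 + SCID 2 + PACOTIS 2 + MIRI 2 + PCOS 1 = 10.
- By the abstract: 3 + 3 + 3 + 2 = 11; with the PCOS added, 12.
- One family per visit: four tests at 3 months (CES-D, SCID, PACOTIS, MIRI) and five at 6 months (these plus the PCOS).

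**2. The plan's 5%.** Under the global null with independent tests, simulated Benjamini–Hochberg family-wise error was 4.9% to 5.0% for 4, 5, 10 and 12 tests. The stated 5% is reproduced in this case.

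**3. A calculation by hand.** Take m independent tests, of which k are real effects certain to be rejected, leaving n = m − k true nulls. Any null with p ≤ a = 0.05(k + 1)/m is then rejected, so the family-wise error is at least 1 − (1 − a)^n.
- m = 4, k = 2: a = 0.0375; 1 − 0.9625² = 7.4%.
- m = 5, k = 2: a = 0.03; 1 − 0.97³ = 8.7%.
- m = 10, k = 5: a = 0.03; 1 − 0.97⁵ = 14.1%.
- m = 12, k = 6: a = 0.0292; 1 − 0.9708⁶ = 16.3%.

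Holm in the third case tests the five nulls at 0.05/5 = 0.01, giving 1 − 0.99⁵ = 4.9%.

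With one true null left, the loosest Benjamini–Hochberg threshold is 0.05 × m/m = 0.05. The family-wise error then cannot exceed 5%.

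**4. Simulation with less certain effects.** I used two-sided z tests, 200,000 runs per scenario and equal correlation between tests. Real effects had an expected z of 2.8 (about 80% power unadjusted) or 4. These effects and correlations are assumptions.

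| Family | Real effects | Correlation 0 or 0.5 | Correlation 0.8 |
|---|---|---|---|
| 4–5 tests | 1–2 | 5.3–8.6% | 4.2–5.6% |
| 10 or 12 tests | 1 | 5.5–8.5% | 3.5–3.9% |
| 10–12 tests | 3–6 | 7.1–15.8% | 4.5–7.0% |
| 4, 5, 10 or 12 tests | all but one | 3.1–4.9% | 2.7–4.3% |

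Holm stayed below 5% in every scenario. A separate run of 100,000 used correlation 0.6 within an endpoint and 0.3 between endpoints. With only the CES-D effective, the pooled family gave 8.3% to 8.4% at an expected z of 2.8 and up to 11.6% with larger effects.

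**5. Cost of Holm.** The two stated detectable effects agree with each other: 0.241 × √(300/240) = 0.269. At Holm's first step the detectable effect is multiplied by (z for 0.05/m, two-sided, + 0.842)/(1.960 + 0.842).

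| Tests | z | Multiplier | 0.241 becomes | 0.269 becomes |
|---|---|---|---|---|
| 4 | 2.498 | 1.19 | 0.287 | 0.321 |
| 5 | 2.576 | 1.22 | 0.294 | 0.328 |
| 10 | 2.807 | 1.30 | 0.314 | 0.350 |
| 12 | 2.865 | 1.32 | 0.319 | 0.356 |

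Later Holm steps are less demanding.

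**The case against.** The best defence is that false discovery rate control may be what the authors wanted, with the error confined to one phrase. Benjamini–Hochberg is a legitimate procedure, it does hold the false discovery rate at 5% in these simulations, and the slip touches neither the estimates nor the confidence intervals. That stands, and it is why relabelling is offered below as a full repair. It does not rescue the sentence, which states a property that the method lacks. This is wrong text, not a detail left to the analysis plan.

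Three stronger readings are not supported.
- **Family-wise error always passes 5% once one effect is real.** It does not when a single true null remains, and it often does not at correlation 0.8.
- **The plan sets up a family of 10 to 12 tests.** No section pools endpoints and visits. Analysing each set of follow-up outcomes separately fits one family per visit just as well, and the excess is then modest. The count of 12 also needs the abstract's visits combined with the PCOS from Table 2.
- **The repair requires a single primary visit or a longitudinal primary model.** Either would change the primary outcomes that the abstract states at several visits, in a trial recruiting since September 2023. Neither is needed to correct this sentence. How the models deal with missed visits is a separate question with no bearing on it.

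**Conclusion.** The concern holds as a mismatch between method and claim. Benjamini–Hochberg does not in general control the family-wise error at 5%, and the setting where it fails, some primary effects real and others null, is a plausible one for this trial. This conclusion does not depend on how many tests the family contains.

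The size does depend on it. It runs from about 5–9% for four or five tests with one or two real effects to about 7–16% for a pooled family with three to six, at correlation 0 or 0.5. A reader might infer that the true rate is two to three times the nominal one. That is reached only towards the upper end of the pooled scenarios, under effects and correlations that the document does not give.

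**What to change.** Choose one of two corrections before the effectiveness outcomes are compared between arms.

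1. If false discovery rate control is intended, state that Benjamini–Hochberg will be used to control the false discovery rate at 5%, and delete the family-wise claim. This costs one sentence. Primary results may then not be described as family-wise protected.
2. If family-wise control of the primary endpoints is intended, replace Benjamini–Hochberg with Holm over the primary tests, which is valid under any dependence. Keep Benjamini–Hochberg for the secondary outcomes, labelled as false discovery rate control.

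Under either option, list the tests that form the family and say whether the MIRI and PCOS count as one test or two. At 6 months this decides between four and five tests.

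The second option costs power, and the plan should say so. At Holm's first step the detectable effect rises by about 19% for four tests, 22% for five, and 30% to 32% if 10 to 12 tests are pooled. The published 0.241 and 0.269 use unadjusted alpha 0.05 and should be labelled as such or restated.

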#### Usual care

Women randomized to the usual family support services/usual care arm will receive Judy Center services without any MB-VG intervention during the study period (but will receive MB-VG after 6 months via our delayed intervention design, if interested). Judy Centers provide an array of services including parenting education, case management, family health and developmental assessments and referrals, and partnerships with childcare and education providers (e.g., Head Start).

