There are several potential challenges and practical issues to consider. First, we expect there will be some degree staff turnover at Judy Centers, turnover is an important and prevalent challenge to scaling and sustaining evidence-based mental health interventions [93]. Given this, we plan to explicitly assess center director perceived barriers to sustainment of the intervention. Challenges recruiting perinatal participants may occur which could lead to lag time between study enrollment and intervention delivery. To minimize attrition and decrease wait time between enrollment and intervention start, we will allow for smaller (e.g., 4–5 participants) intervention cohorts and for cohorts combining individuals from across Judy Centers. The virtual format facilitates combining individuals from across Judy Centers; with the impact of blended versus single-center cohorts on effectiveness and implementation explored through our qualitative data collection activities. Additionally, as multiple Judy Center staff will be trained on MB-VG, it is possible they will use intervention language and activities during their work with participants randomized to the usual care arm. Study investigators have successfully addressed this in previous trials by clearly communicating study protocols to all agency staff. Moreover, our delayed intervention design means that control participants will be able to receive MB-VG thus minimizing concern among staff that participants will not benefit from intervention content.

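### The Aim 1 model uses instructor terms that usual-care participants cannot have, gives MB-VG cohorts no clustering term of their own, and lets significance tests remove its terms

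*Protocol article*

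**What the plan says.** The Quantitative analysis section tests Aim 1 by the coefficient of the arm indicator in a mixed model.

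- Random part: "We will include random intercepts for group and instructors". The authors "will also investigate whether a random slope for group is appropriate for the intervention effect".
- Fixed part: arm, pretest covariates, and also "the Judy Center the participant was recruited from, and instructor characteristics will be included as fixed effects".
- Clustering unit: the same section describes "participants clustered by group (i.e., Judy Center").
- Reduction: likelihood ratio tests at p<0.05 "will be used to simplify the models following a backward selection strategy". No term is named as exempt.

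Three other places bear on this. Under MB-VG, each cohort is led by two Judy Center staff. Under Usual care, controls "will receive Judy Center services without any MB-VG intervention during the study period". The Discussion allows small cohorts of 4-5 and provides "for cohorts combining individuals from across Judy Centers".

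The article defers the final covariate list to a statistical analysis plan. It does not defer the random effects, the instructor terms or the selection rule.

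**The concern.** Randomization is by individual, and only one arm is then treated in groups. A model for that design has to say what each term means for a woman who never joins a group.

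- **Instructor terms.** They describe MB-VG facilitators. A usual-care participant has no facilitator during follow-up, and the article gives no rule for coding her. Which facilitator a woman receives is also settled after randomization and in one arm only, so facilitator characteristics do not belong among the adjustments in an intention-to-treat contrast.
- **Group.** As defined, it is the Judy Center, which is already a fixed effect. The unit that shares sessions and facilitators is the MB-VG cohort. Because cohorts may draw on several centers, center cannot stand in for cohort.
- **Selection.** Backward elimination applied to the confirmatory model can discard the clustering term and weak covariates, and can do so differently for each endpoint and visit.

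At stake are the meaning and the standard error of the coefficient that decides Aim 1.

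**Working it through.** **1. The plan's own figures.** Minimal detectable effect = (t₀.₉₇₅ + t₀.₈₀) × √[(1−R²)/(0.25N)].

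- With R² = 0 this gives 0.325 at N = 300 and 0.363 at N = 240, against the stated 0.241 and 0.269.
- With R² = 0.45 it gives 2.811 × √(0.55/75) = 0.241 and 2.813 × √(0.55/60) = 0.269. The two figures are coherent given a covariate R² that the article does not print.
- The clustered figure implies a design effect of (0.284/0.241)² = 1.389. If all participants are clustered, ICC = 0.389/(m−1): 0.097 for m = 5, 0.056 for m = 8, and 0.016 for m = 25 (300 women over 12 centers). The article states neither ICC nor m, so the figure does not show which unit was meant.

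Nothing below depends on these figures.

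**2. Instructor characteristics, two codings.**

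- *Missing for controls.* A complete-case fit keeps only MB-VG women. The columns for intercept, arm and covariate then have rank 2 of 3, because arm equals the intercept. The arm effect is not estimable.
- *Coded 0, uncentred.* The arm coefficient becomes the effect at a covariate value of 0. With 150 per arm its variance is multiplied by 1 + x̄²/(2s²). For an assumed covariate with mean 5 and SD 3 this is 1 + 25/18 = 2.39. A simulation with 13 facilitators, values truncated at 0, gave a median of 2.71, a standard error about √2.71 = 1.65 times as large.

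**3. Judy Center both random and fixed.** In 200 simulated trials with 12 centers of 25, the arm estimate matched the model with fixed centers alone to within 10⁻¹⁵, and the ratio of standard errors was 1.000. The center variance is not identified, but the arm comparison is unaffected.

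**4. Cohort clustering and selection.** Simulation under no effect: 150 controls, about 150 MB-VG women (30 cohorts of 5 or 18 of 8), clustering in the MB-VG arm only, 4,000 trials per row, normal critical values, and a drop rule of likelihood ratio statistic below 3.84. ICC and cohort size are assumptions. There were no covariates and no attrition. Monte Carlo standard error is about 0.003-0.004 near these rates.

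| Cohort size | ICC | Cohort term always kept | Term pruned by test | Clustering ignored | Term dropped |
|---|---|---|---|---|---|
| 5 | 0 | 0.048 | 0.052 | 0.052 | 98% |
| 5 | 0.02 | 0.049 | 0.054 | 0.055 | 97% |
| 5 | 0.05 | 0.052 | 0.062 | 0.066 | 90% |
| 5 | 0.10 | 0.056 | 0.066 | 0.079 | 73% |
| 8 | 0 | 0.044 | 0.050 | 0.050 | 98% |
| 8 | 0.02 | 0.044 | 0.051 | 0.052 | 95% |
| 8 | 0.05 | 0.049 | 0.062 | 0.067 | 87% |
| 8 | 0.10 | 0.061 | 0.076 | 0.097 | 65% |

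Entries other than the last column are type I error. Treating each control as a cluster of one gave 0.043-0.059 over the same settings.

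Formula check on the ignored column: variance factor = [1 + (m−1)ICC + 1]/2, and type I error = 2[1 − Φ(1.96/√factor)]. For m = 5, ICC 0.05 the factor is 1.10 and the error 0.062. For m = 8, ICC 0.10 they are 1.35 and 0.092. Both are close to the simulated values.

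**The case against.** A reader might infer that the model cannot validly be fitted at all. The documents do not support that. Entering center twice does not alter the arm estimate, and random effects confined to one arm can be fitted with near-nominal error.

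Nor do the two complaints about group hold together. If group is the Judy Center, as the article says and as a random slope for the intervention effect requires, controls do have a group and the fault is redundancy. If group is the MB-VG cohort, controls have none, but then center is not entered twice.

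A reader might also expect the analysis to lose all 150 controls. That is what software does by default with missing values, not what the article plans. It commits to intention-to-treat, and an empty arm would be noticed. The realistic danger is an improvised coding.

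A type I error of 10.4% can be derived by ignoring clustering outright with cohorts of 10 and an ICC of 0.10 (factor 1.45). The article supports neither input and expects clustering to be very small. An instructor intercept, if kept, would also absorb part of the cohort effect.

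Loss of a strong baseline score is unlikely. With 240 women analysed and an assumed baseline R² of 0.10, the statistic is −240 × ln(0.90) = 25.3 against 3.84. By the footnotes to Table 2, the SCID, PACOTIS and MIRI have no baseline value to drop.

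Finally, coding detail can be left to an analysis plan. That is fair for the coding alone. It does not cover an instructor adjustment and a selection rule that the article states as settled.

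**Conclusion.** The primary model is partly mis-specified as written.

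- The instructor random intercepts and characteristics have no meaning for controls before the 6-month endpoint. Followed literally, the characteristics leave the arm coefficient either not estimable or reinterpreted. This rests on the text alone.
- MB-VG cohorts lack a clustering term of their own. The duplicated center term is untidy but harmless.
- Backward selection can remove the clustering term and named covariates. The inflation is moderate: about 6.2% at ICC 0.05 and 6.6-7.6% at ICC 0.10, for assumed cohorts of 5-8. At ICC 0.02 or below it is negligible (5.0-5.4%).

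The sizes depend on assumed ICCs and cohort sizes. Because this model decides Aim 1 and the correction is cheap, it should be made before outcome data are analysed.

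**What to change.** State one pre-specified partially nested model for each primary endpoint and visit:

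- **Fixed effects:** arm, the baseline value of the outcome where it is collected, the named covariates, and Judy Center entered once.
- **Random effects:** an intercept for MB-VG cohort in the MB-VG arm only, with each control as her own unit, and small-sample degrees of freedom.
- **Facilitators:** the article lets a facilitator lead more than one cohort, so a cohort term alone may miss some correlation. Add a facilitator-level term in the MB-VG arm, or a sensitivity analysis that includes one.
- **Instructor characteristics:** remove them from the arm comparison and use them in within-arm analyses for Aims 2 and 3.
- **Selection:** delete it. Keep the covariates and the cohort term whatever their p-values.

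The cost is a change of wording and slightly wider intervals. Cohort membership should be recoverable from the session attendance logs.
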